#### Measures of safety (primary study outcomes)

a) Number of missed cervical spine injuries, i.e. number of clinically important c-spine injuries (as defined previously) identified in patients who have had their c-spine cleared by paramedics. We will know the presence of fracture or cervical spine injury from review of diagnostic imaging reports in the patient record. We also propose to institute a strategy of surveillance to identify the uncommon occurrence of a fracture missed because no radiography was ordered. ED Patient Visit Logs at each receiving hospitals will be monitored for 30 days to identify return visits by patients who do not undergo radiography during their initial ED visit. In addition, we will review the Neurosurgery Patient Logs at our regional neurosurgical centre (The Ottawa Hospital, Civic Campus). This centre provides care for patients with spinal cord injuries for the whole Ottawa region. We recognize that there is a very small risk of not identifying a missed fracture but feel that this approach is pragmatic and feasible.

b) Number of serious adverse outcomes, i.e. development of neurological deficit after c-spine clearance by the paramedics. This very unlikely subset of missed cervical spine injury cases will be determined from review of the patient records. We will monitor for the extremely rare occurrence of motor weakness and disability that develops after paramedic assessment but do not expect this to occur.

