We evaluated current physician practice, without the use of the CCR, by noting the number of cases where patients with cervical spine fractures were discharged from the ED without the fracture having been identified. This occurred 14 times during the study and nine of these cases were clinically important cervical spine injuries. All these patients returned due to ongoing pain or were recalled by the radiology department one or more days after the initial ED visit. Fortunately, no patient suffered an adverse outcome. In one of the nine clinically important cervical spine injury cases, no radiography was ordered during the initial visit. In another seven of the nine cases, physicians misread the radiographs as normal and the radiologists subsequently identified the error. In the ninth clinically important cervical spine injury case, the initial radiograph was actually normal.

Results from phase IIIa, which took place in 12 Canadian EDs from 2004 to 2006 (n = 11,824 patients) were recently published [76]. Phase IIIa was a matched-pair cluster design trial which compared outcomes during 12-month 'before' and 'after' periods at six 'intervention' and six 'control' EDs, stratified by teaching or community hospital status. All alert, stable adults presenting after acute, blunt head or neck trauma were enrolled. Sites were randomly allocated to either intervention or control groups. During the intervention-site after-period, active strategies were employed to implement the CCR into practice, including education, policy, and 'on-line' reminders. Outcomes included cervical spine imaging rates and missed injuries. From the before to after periods, the cervical spine imaging rate had a *relative reduction *of 12.8% at the six intervention sites from 61.7% to 53.3% (P = 0.01) but a *relative increase *of 12.5% at the six control sites from 52.8% to 58.9% (P = 0.03); this difference between groups was significant (P < 0.001). There were no missed c-spine injuries at the intervention sites. We concluded that, despite low baseline cervical spine imaging ordering rates, active implementation of the CCR by physicians led to a significant decrease in use of cervical spine imaging without missed injuries or patient morbidity. Widespread use of the CCR for clinical clearance of the c-spine could lead to reduced health care costs and more efficient patient flow in busy EDs.

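### The 30-day return-visit search leaves out imaged patients, so a clinically important injury behind a truly normal first film has no planned emergency department follow-up

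*Protocol article*

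**What the plan says.** Under Measures of safety (primary study outcomes), item a), the protocol article counts clinically important injuries in patients whose c-spine was cleared by paramedics. It names three sources.

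- Imaging reports: "We will know the presence of fracture or cervical spine injury from review of diagnostic imaging reports in the patient record".
- ED visit logs at the receiving hospitals, monitored for 30 days. The stated aim is "to identify the uncommon occurrence of a fracture missed because no radiography was ordered", and the search is set up "to identify return visits by patients who do not undergo radiography during their initial ED visit".
- Neurosurgery logs: "In addition, we will review the Neurosurgery Patient Logs at our regional neurosurgical centre". This source is not limited by imaging status.

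The same item accepts a very small risk that a missed fracture goes unidentified. Under Data collection, study personnel also review daily patient logs, ED records, imaging reports and in-patient records, but no 30-day search is described for patients who were imaged. Under Data analysis, Measures of safety, the missed-injury rate is expected to be 0%.

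**The concern.** The return-visit search rests on the premise that an injury is overlooked because no film was taken. The Background section on previous physician studies shows that this is not the only route: "In the ninth clinically important cervical spine injury case, the initial radiograph was actually normal". A cleared patient with that history would carry a negative first imaging report and would not be on the list matched to the ED logs.

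At stake is the direction of the error. The outcome is a count expected to be zero, and incomplete ascertainment can only make it smaller. The Rationale makes wider dissemination depend on this study showing safety, so even one uncounted case would affect how the result reads.

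**Working it through.** **Routes in the article's own data.** In the phase II physician validation study, fractures were overlooked at ED discharge as follows: "This occurred 14 times during the study and nine of these cases were clinically important cervical spine injuries". By route, 1 (no film) + 7 (film misread) + 1 (film truly normal) = 9, which agrees with the stated total.

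**Each route against the planned sources.**

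| Route | Cases | First imaging report | 30-day ED log search |
|---|---|---|---|
| No film ordered | 1 | nothing to review | covered |
| Film misread by ED physician | 7 | covered: "In another seven of the nine cases, physicians misread the radiographs as normal and the radiologists subsequently identified the error" | not covered, not needed |
| Film truly normal | 1 | negative | not covered |

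The imaging reports and the search together cover 7 + 1 = 8 of 9 (89%, exact 95% CI 52 to 99.7%). The gap is the remaining 1 of 9 (11%, CI 0.3 to 48%).

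**How such a case comes to light.** On the overlooked cases the article says: "All these patients returned due to ongoing pain or were recalled by the radiology department one or more days after the initial ED visit". A truly normal film gives radiology no misreading to correct, so a return visit is the likelier route of discovery (an inference). That is the event not searched for in imaged patients.

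**The remaining backstop.** The neurosurgery log belongs to one centre, described by its care of spinal cord injury. The definition of a clinically important injury also takes in those treated with a brace or rigid collar, and these need not appear in that log.

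**Expected number.** Inputs: 162 clinically important injuries in phase II, of which the rule identified 161; 20 such injuries expected here (Sample size). Assume that the nine cases are among the 162 and that the normal-film rate carries over.

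- Among all injured patients: 20 x 1/162 = 0.12. The exact 95% CI for 1/162 is 0.016% to 3.4%, which gives 0.003 to 0.68.
- A counted miss must also have been cleared. If clearing were independent of the film and as rare as the rule's one miss in phase II: 0.12 x 1/162 = 0.0008.
- With the lower confidence limit for sensitivity in paramedic hands, 74%: 0.12 x 0.26 = 0.03. At the upper rate limit: 0.68 x 0.26 = 0.18.

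Independence is an assumption. If subtle injuries tend both to pass the rule and to show a normal film, the number is higher, but at the point estimate it cannot exceed 0.12.

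**What one case would change.** If 40% of 3,000 patients are cleared, the denominator is 1,200. With no misses the exact upper 95% limit is 1 - 0.025^(1/1200) = 0.31%. With one miss it is 0.46%.

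**The case against.** The strongest reply is that the nine cases concern a different event. They were overlooked by ED physicians in usual practice, not by the rule, and the article does not say that any was rule-negative. If they are among the 162 injuries, at most one can have been. This stands, and it is why the expected number is so small. It does not restore the premise, because the search covers only one of the two routes that a first imaging report cannot reveal.

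The second reply is that other sources exist and that the limit is disclosed. This stands in part. The neurosurgery log already applies whatever the imaging, in-patient records are reviewed, and imaging reports are not expressly confined to the first visit. But for an imaged patient, discovery in ED or imaging records depends on someone happening to review a later record. The acknowledgement of residual risk does not mention a normal first film.

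Two stronger readings are tempting. A reader might infer that eight of the nine recorded cases would escape, since eight had a film. The article does not support this: radiologists identified the seven misreadings, and injury status is taken from imaging reports. A reader might also infer from the paramedic validation study, where 2,393 - 1,126 = 1,267 patients (53%) were imaged, that about half of cleared patients go unascertained. That share is for all enrolled patients in a study where everyone was immobilised. The share among cleared patients is not given, and imaged patients do have imaging, the main means of ascertainment.

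**Conclusion.** The point holds in a narrow form. The radiography condition leaves one route to a missed clinically important injury, recorded in the investigators' own physician study, outside both the first imaging report and the 30-day search. The gap is 1 of the 9 recorded cases. The expected number here is well below 0.12, on the assumptions that 1/162 carries over to 20 injuries and that few injured patients are cleared.

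A reader should not infer that the safety result would probably be wrong, or that such a patient would come to harm. The article reports no adverse outcome among the overlooked cases and describes them only as clinically important. The reason to act is that the error runs in one direction, in a primary count expected to be zero, and is cheap to remove.

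**What to change.** In Measures of safety, item a), delete the radiography condition so that the 30-day ED log match covers every patient cleared by paramedics, whatever imaging was done at the first visit. Do not narrow the search for anyone it now covers. State that clinically important injuries shown on return-visit imaging count as missed injuries. The neurosurgery log review needs no change.

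The cost is a longer list of patients to match against logs already monitored at the receiving hospitals, and a count that may be less favourable. The comparison with the validation study loses no matched method, because that study already used a different follow-up: a telephone assessment at 14 days for patients without radiography.

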#### Measures of clinical impact (primary study outcomes)

a) Proportion of low-risk patients transported without immobilization, i.e. proportion of eligible trauma patients who are not immobilized by paramedics. Daily EMS patient census logs will be reviewed to identify potential neck injury patients and then ED patient records (including ambulance call reports, nursing notes, and physician notes) will be assessed to determine eligibility. All eligible patients assessed by participating paramedics will be considered for the denominator of this measure. We will also report the number of eligible patients not assessed.

b) Lengths of time, i.e. time spent in the field before transport, time from ED arrival to transfer of patient care to ED staff; and total patient length of stay in the ED. These times will be compared, for those patients transported with and without spinal immobilization as part of the evaluation phase of this study, to those transported with immobilization (100% cases) during the validation study at the Ottawa site. We will only measure times for those patients who are assessed and enrolled by the paramedics.

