### Cervical spine immobilization

Because of the potential for spinal injury, paramedics go to great lengths to protect the cervical spine of trauma patients. Consequently, regardless of the presence of neck symptoms, most trauma victims transported to hospital in ambulances are protected by such measures as a backboard, collar, and head immobilization devices [4,22]. Not only is this often unnecessary, the potential for clinical adverse effects and discomfort from immobilization have been well documented. Chest straps used in immobilization have a marked pulmonary restrictive effect, even in healthy non-smokers [38]. Immobilization on a board leads to progressively worse pain in the head, neck, and back area, often resulting in the necessity to radiograph an otherwise normal spine in the ED [39-41].

Because trauma victims should be seen rapidly at the hospital, paramedics are given only 15-20 minutes to evaluate and treat them in the field before transport. Even for minor trauma victims, cervical spine immobilization takes at least five minutes to apply, or up to 30% of the allowed field time. Unlike minor trauma victims coming to the ED using their own means of transportation, who are most commonly sent immediately to the waiting room area, similar trauma victims immobilized and transported by paramedics can wait up to three hours until an ED stretcher becomes available, also holding up the EMS crew who then becomes unavailable for the next community emergency.

Once on an ED stretcher, it is not unusual for these patients to remain with full immobilization for several hours until c-spine radiographs or computed tomography can be performed and interpreted. As well, efforts to obtain satisfactory c-spine radiographs often require repeated attempts. This consumes valuable time for physicians, nurses, and radiology technicians and distracts them from other urgent responsibilities [15,42]. In addition, this delay compounds the burden of our crowded Canadian EDs in an era when they are under unprecedented pressures [42-44]. The median length of stay for a patient evaluated in the stretcher area is approximately eight to 12 hours, whereas similar minor trauma victims arriving without immobilization can be evaluated and discharged in less than four hours from the waiting room area.

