### Validation of the CCR by paramedics

The validation of the CCR by paramedics took place between 2002 and 2006 in seven EMS systems distributed in three Canadian provinces [77]. The study population consisted of consecutive alert, stable, and cooperative adults transported by ambulance to the local lead trauma hospital after sustaining acute blunt trauma with potential injury to the neck. These are patients for whom standard basic trauma life support (BTLS) protocols require immobilization. Patient assessment was made by primary care or advanced care paramedics, who were trained by means of a 2-hour web-based training session followed by a practical demonstration to assess the CCR and the component clinical variables in a uniform manner. The paramedics recorded their findings along with their interpretation of the decision rule itself on a data collection form prior to arrival at hospital. They followed standard procedures for immobilization of patients and did not use the CCR as the basis for the decision to immobilize. The primary outcome, acute cervical spine injury, was defined as any fracture, dislocation, or ligamentous instability demonstrated on radiography. A clinically important cervical spine injury was defined as any injury requiring internal fixation or treatment with a halo, brace, or rigid collar. All enrolled patients who did not have radiography received telephone follow-up and were classified as having no acute cervical spine injury if they met all the previously validated explicit criteria at 14 days [78].

We enrolled 2,393 eligible patients in the study. 1,126 patients were not evaluated with radiography, and required telephone follow-up. We reached 788 (70.0%) of those patients, among which 682 were determined to not have sustained a cervical spine injury according to our validated proxy assessment tool. A total of 1,949 enrolled patients had complete outcome assessments. Twelve (0.6%) had a clinically important cervical-spine injury. In two cases, the investigators could perform an independent assessment of the rule based on the paramedic care report, but could not evaluate the paramedic assessment of the rule based on their study data collection sheet. The characteristics of the 444 patients without outcome assessments were similar to those with radiographic evaluation, but were less likely to be admitted to the hospital.

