#### Comparison Group from the Validation Study

We will quantify the potential impact of selective prehospital immobilization by way of comparison with a convenience sample of patients recruited in Ottawa during the validation of the CCR by paramedics between 2002 and 2006 [77]. These participants were recruited using the exact same criteria, and represent 862 of the 1949 recruited in the validation study [77].

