#### Measures of clinical impact

a) Proportion of low-risk patients transported without immobilization will be described as overall proportion with 95% confidence intervals, based upon a denominator of patients actually assessed by participating paramedics as judged by the completion of a Paramedic Data Form. This will be compared to the immobilization rate in the validation study, which we know to be close to 100% since paramedics were required to immobilize all patients by protocol.

b) Lengths of time will be presented as means plus standard deviations. We will compare time intervals for those patients assessed as part of the evaluation phase of this study, to those assessed during the validation study at the Ottawa site using the Student's t-test.

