### Sample size

Sample size estimates for this study are governed by a number of considerations related to the various outcome measures (safety, clearance rate, accuracy) as well as feasibility. Our overall goal is to enroll patients in this evaluation study for 36 months, following the (up-to) six-month run-in period. Our future Phase IV implementation trial will have much larger patient numbers and more robust estimates of effect but we must demonstrate safety and efficacy first in this preliminary study. The results of this evaluation study will inform the design and sample size estimates for the future definitive Phase IV trial. Based upon the Paramedic Validation study, we expect that 380 paramedics will participate in the evaluation study and that 3,000 patients can be enrolled over 36 months. The consensus of the investigators is that this will give us an adequate number of cases in which to evaluate safety, clearance rates, and accuracy. We expect that 20 enrolled patients will have clinically important cervical spine injury. For clinical impact, we anticipate that as much as 40% of all patients assessed could be transported without full cervical spine immobilization.

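### The primary time-interval comparison is worded in two ways: one mixes risk selection with the effect of clearance, and both leave change since 2002-2006 unadjusted

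*Protocol article*

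**What the plan says.** Lengths of time (field time, time to transfer of care, total ED stay) are listed in the protocol article under Measures of clinical impact (primary study outcomes). There the comparison is made "for those patients transported with and without spinal immobilization as part of the evaluation phase of this study, to those transported with immobilization (100% cases" at the same site in the validation study.

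Under Data analysis, Measures of clinical impact, the wording has no split by immobilization: "We will compare time intervals for those patients assessed as part of the evaluation phase of this study", set against "to those assessed during the validation study at the Ottawa site using the Student's t-test".

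The section Comparison Group from the Validation Study describes the comparator as a "convenience sample of patients recruited in Ottawa during the validation of the CCR by paramedics between 2002 and 2006", says that the same criteria were used, and adds that these patients "represent 862 of the 1949 recruited in the validation study". For the new study, the Sample size section expects that "3,000 patients can be enrolled over 36 months", with up to 40% transported without full immobilization.

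Rule status is available from the validation study. Its description states: "The paramedics recorded their findings along with their interpretation of the decision rule itself on a data collection form prior to arrival at hospital". In the new study the investigators make a criterion interpretation of the rule from the paramedic's form.

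**The concern.** In the validation study everyone was immobilized by protocol, whatever the risk. In the evaluation period the rule, subject to paramedic override, decides who is immobilized. A group defined by actual immobilization in the evaluation period is therefore selected on risk, and the validation cohort is not. If low-risk patients have shorter stays for reasons unrelated to the collar and board, a contrast by immobilization status shows a difference even when clearance changes nothing.

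On either wording the reference group is historical and the test is unadjusted. The article links these intervals to ED crowding. It also describes the validation patients as taken to the local lead trauma hospital, whereas the safety section for the new study speaks of several receiving hospitals. In addition, the 1,949 from which the 862 are drawn are the patients with complete outcome assessments. A further 444 were enrolled without them and were less likely to be admitted, which bears on ED stay.

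At stake is the reading of a primary efficiency outcome in a study that the Rationale says must show both safety and efficacy before dissemination.

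**Working it through.** **Inputs from the article.** Evaluation n = 3,000; comparator n = 862; up to 40% cleared (Sample size); 62.2% requiring immobilization under the rule (Validation of the CCR by paramedics). No SD, alpha or target difference is given for the time intervals. I assume two-sided 0.05 and SDs of 120, 180 and 240 min for ED stay.

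**The plan's own share.** 1 - 0.622 = 0.378, consistent with up to 40%. That is 0.378 x 3,000 = 1,134, or 0.40 x 3,000 = 1,200 patients.

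**Contrast by immobilization status, no true effect.** Let p be the low-risk share and g the amount by which the mean stay of other patients exceeds that of low-risk patients.
- Cleared minus all validation = -(1-p)g
- Immobilized minus all validation = +pg
- Pooled minus all validation = p x [-(1-p)g] + (1-p) x pg = 0

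With p = 0.40, the last column gives the chance that the cleared-versus-validation test (1,200 vs 862) is falsely significant. It is a normal approximation with SE = SD x sqrt(1/1,200 + 1/862).

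| Assumed g (min) | Cleared | Immobilized | False significance at SD 120 / 180 / 240 |
|---|---|---|---|
| 15 | -9 | +6 | 39% / 20% / 13% |
| 30 | -18 | +12 | 92% / 61% / 39% |
| 60 | -36 | +24 | 100% / 99% / 92% |
| 109.7 | -65.8 | +43.9 | 100% / 100% / 100% |

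The last row uses 232.9 - 123.2 = 109.7 min from the physician validation study. That figure compares patients with and without radiography, not rule-positive with rule-negative patients, so it is only an upper illustration.

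**Pooled contrast, no true effect, calendar drift d.** SE = SD x sqrt(1/3,000 + 1/862), which is 6.96 min at SD 180. The chance of significance at SD 120 / 180 / 240 is:
- d = 10 min: 58% / 30% / 19%
- d = 20 min: 99% / 82% / 58%
- d = 30 min: 100% / 99% / 90%

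**Field time.** The article says that immobilization takes at least five minutes. If five minutes were saved in 40% of patients, the pooled saving would be 0.40 x 5 = 2 min. A drift of 1 min alone would be significant with probability 99%, 90% or 73% at assumed SDs of 6, 8 and 10 min.

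**Precision of a like-with-like analysis.** Applying 37.8% to the comparator gives 0.378 x 862 = 326 rule-negative and 536 rule-positive patients, assuming that Ottawa matches the whole validation study.
- Rule-negative evaluation vs rule-negative validation, SD 180: SE = 180 x sqrt(1/1,134 + 1/326) = 11.3 min. The difference detectable at 80% power is about 32 min (21 and 42 min at SD 120 and 240).
- Period by rule status, SD 180: SE = 180 x sqrt(1/1,134 + 1/1,866 + 1/326 + 1/536) = 14.3 min.

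These standard errors ignore the 320 of 1,949 validation patients (16.4%) whose rule status was indeterminate. Specificity there ran from 32.4% to 46.6% according to how they were coded, so the split of the comparator is uncertain.

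**The case against.** The strongest reply is that patients with and without immobilization together make up the whole evaluation cohort. Read that way, the outcome section agrees with the data analysis section, which names the test, and with the Design section, which compares outcomes between periods. The pooled contrast is then a legitimate service-level question and is free of the selection problem if case-mix is stable. This stands. A reader might infer that the plan as written must produce a spurious saving and a spurious lengthening, but the text does not support that. It follows only if groups are formed by immobilization status, and the wording leaves this open.

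A reader might also infer that drift would favour clearance. The article says that EDs are under pressure, but it reports no trend since 2002-2006 and gives no evaluation dates. Worsening crowding would lengthen evaluation stays and hide a saving.

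A third tempting step is to take the 109.7 min radiography gap as both the risk gap and the effect of clearance, and to scale drift against it. Both cannot hold: 123.2 - 109.7 would leave a stay of 13.5 min. Those stays also fit poorly with the Background statement that "The median length of stay for a patient evaluated in the stretcher area is approximately eight to 12 hours".

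Finally, the article discloses the convenience sample, states that site and criteria are the same, calls the study preliminary, and defers more robust estimates to a later trial. Covariate adjustment is often left to an analysis plan. These points lower the severity but do not remove the concern: the article itself fixes the contrast, the comparator and an unadjusted test, in two wordings that can be read differently.

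**Conclusion.** The point holds at moderate severity. The two sections need to be reconciled.

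Under a split by immobilization status, the bias with no effect is -(1-p)g for cleared and +pg for immobilized patients: -18 and +12 min at p = 40% and an assumed 30 min gap. Under pooling, the selection bias is zero if case-mix is stable and the estimand is valid. Drift since 2002-2006 and differences in receiving hospital or cohort make-up then enter in full.

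The formulas are exact. The gap, the SDs and the drift are assumptions, and the size and direction of drift cannot be derived from the article.

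**What to change.** 1. State one policy-level estimand in both sections: all evaluation versus all validation patients. Do not compare groups defined by actual immobilization with the whole validation cohort.
2. Add a comparison within the investigators' criterion rule status: rule-negative evaluation versus rule-negative validation patients, with the rule-positive contrast beside it as a check on drift. Alternatively, report period by rule status as the drift-corrected estimate.
3. Adjust for age and arrival time, and adjust for receiving hospital or restrict to the hospital common to both periods.
4. Analyse the indeterminate validation patients both ways, as rule-positive and as rule-negative.
5. Because overrides occur, describe the result as the effect of the clearance policy in rule-negative patients.
6. State the assumption that rule-positive and rule-negative patients share the same drift. If freed stretchers also shorten rule-positive stays, the interaction estimate is conservative.

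The cost is analysis work, including the coding of indeterminate patients, since rule findings were recorded in both studies. The price in precision is a wider standard error: about 14 min for the interaction if the SD is 180 min and indeterminate patients are ignored, against about 7 min for the pooled contrast.
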